## Abstract

**Background:**

Indigenous communities in Canada face significant challenges with intergenerational trauma, which manifests in substance use disorders. There is consensus that connecting treatment approaches to culture, land, community, and spiritual practices is a pathway to healing trauma and substance use disorders for Indigenous peoples. Indigenous residential addiction treatment programs have been established as the primary intervention to provide healing for Indigenous peoples with substance use disorders and intergenerational trauma. However, there is limited evidence demonstrating the effectiveness of these programs. In collaboration with the Benbowopka Treatment Centre, this paper describes a study protocol which aims to evaluate the effectiveness of blending Indigenous Healing Practices and Seeking Safety for the treatment of Indigenous patients with intergenerational trauma and substance use disorders.

**Methods:**

We will conduct a pre/post Quasi Experimental Community trial, to compare historical treatment outcomes for patients following the implementation of Indigenous Healing and Seeking Safety. We will conduct quantitative and qualitative analyses to understand the differences before and after the intervention is implemented. The pre- Indigenous Healing and Seeking Safety intervention study window will span from 2013 to 2016; *n* = 343, and the post-Indigenous Healing and Seeking Safety intervention study window from 2018 to 2020; *n* > 300. All participants will be enrolled in the Benbowopka residential treatment for the first time during the study periods. All data will be anonymized at the time of data entry. Propensity matching will be undertaken for patient characteristics, including sex/gender, age, and substance use type.

**Results and conclusions:**

The study findings could be used to inform intergenerational trauma and substance use disorders residential treatment programming for Indigenous communities across Canada. Our work will contribute to the field of community-based intergenerational trauma and substance use disorders programming by addressing objectives that consider: (a) the patient perspective, (b) the program perspective, and (c) the community perspective. The study findings may validate an innovative approach for evaluating the effectiveness of residential addiction treatment and particularly the effective and appropriate care for Indigenous patients with intergenerational trauma and substance use disorders.

## Background

Approximately 474 000 Indigenous people live in 617 First Nations communities across Canada; 125 of those communities are located in Ontario, primarily in rural and remote areas [1]. The remoteness of these communities, as well as rural health challenges, coupled with the lack of traditional and culturally sensitive treatment models pose huge challenges for the treatment of intergenerational trauma (IGT) [2–5]. These factors have strongly contributed to the multigenerational grief and loss associated with IGT [5–8].

Today, many Indigenous communities affirm that their healing and wellness is embedded in reclaiming cultural and Spiritual interventions. These include traditional teachings, presence of Elders, sweat lodges, prayers, fasting, and sacred song and dance [9–12]. Indigenous treatment programs in urban and regional areas integrate these cultural practices into programs [13]. In Canada, for example, the 56 National Native Alcohol and Drug Abuse Programs (NNADAP) and nine Youth Solvent Addiction Program treatment centers support and encourage Indigenous traditional healing practices and culture as an integral part of health, wellness, and healing [14]. These programs are overseen by First Nations communities and support a network of residential treatment and community prevention programs practicing Indigenous traditional healing practices, Spirituality and creation stories [15–17].

Between 2004 and 2009, the number of Indigenous patients seeking treatment for substance use disorders (SUD) in Ontario increased threefold [18]. The Chiefs of Ontario have identified opioid use disorder as a health priority as the number of people seeking treatment continues to climb (Chiefs of Ontario, 2009). Many Elders, traditional healers, and Indigenous scholars agree that connecting to culture, land, community, and spiritual practices is a pathway to healing IGT and substance use disorders (SUD) for Indigenous peoples [19–21]. The skills required to heal from IGT and subsequent recovery of identity can be enhanced by cultural practices, Indigenous Healing (IH), the presence of Elders, and traditional ceremony [5, 20, 20, 22, 23].

Outpatient and residential treatment of SUD within Indigenous communities presents many challenges and barriers [2, 24]. Many communities continue to report the need for increased access to evidence-based treatment options [25, 26]. While it appears as though some success has been achieved by treatment models [24, 27, 28]; there is a lack of access and a need for evidence-based treatments [24, 27, 28]. Many communities report a lack of services, specifically Indigenous treatment options and culturally sensitive approaches, as well as a lack of cultural awareness from health care professionals and rehabilitation services [25]. Moreover, there is currently limited knowledge in regard to how well the existing services and treatment centers in northern Ontario are addressing the needs of young people with SUD.

In Canada, there are 49 federally funded adult and youth NNADAP and nine YSAP treatment centres. The majority of NNADAP centres were founded on Western approaches to treatment in the 1980s, and later incorporated Indigenous understandings of healing and personal growth. Therefore, to date the majority of addiction treatment for Indigenous populations in Canada is residential treatment [14]. An addictions service needs assessment study conducted in Ontario First Nations communities—the majority of which were located in northern Ontario—reported that the addiction-related education, promotion and prevention programs in their communities mainly targeted adults [29, 30]. These communities also report the effects of both IGT and SUD and the need for culturally based and culturally safe services, particularly those that are informed by institutional IGT experienced by Canada’s First Nations, Métis and Inuit peoples [29, 31].

De Andrade et al. 2019 conducted a systematic review of all studies on the effectiveness of residential treatment published between January 2013 and December 2018 [32]. They identified that despite the growing need for effective residential SUD treatment internationally, there was a lack of consensus on best practice treatment guidelines. In line with previous reviews, this review is of the most recent studies in the field (2013–2018) and provided some evidence that residential treatment may be effective in reducing substance use and improving mental health [32]. Furthermore, the authors found evidence that treatment may have a positive effect on social and offending outcomes. This research also identified an urgent need to conduct more research in this field that could address significant methodological flaws, and affirm that these flaws could be partially overcome by the use of data linkage practices to monitor outcomes [32]. Of note, there was an absence of evidence evaluating the impact of residential addiction treatment on broader health system utilization.

In a recent paper by Munro et al. 2017, the authors identified that residential rehabilitation is not just about length of time and client characteristics in treatment. Culture, ceremony, activities and connections were also integral to the therapeutic healing process and these activities were found to enhance positive change in clients over time [33]. Furthermore, this study reported that the cultural elements offered hope and healing for clients in a remote Indigenous residential addiction treatment program [33].

Other researchers and authors affirm that effective, culturally safe residential rehabilitation services for Indigenous peoples are crucial to enhance recovery and success in treatment outcomes [34]. However, research, evaluation and science inquiry requires a sound theory in combination with rigorous testing and validation of tools. There is a lack of this required evidence in the Indigenous addiction treatment literature. Such studies in Indigenous populations have been criticized due to a reliance on small sample sizes [16, 35].

Recent work from [name] has demonstrated that Indigenous and Western approaches for the treatment of Indigenous patients with a history of IGT and SUD could be effectively combined with positive results using the Indigenous Healing and Seeking Safety (IHSS) approach [24, 36]. The Western Model, Seeking Safety (SS), is a psycho-educational counseling program that targets the unique problems resulting from SUD and IGT [37]. SS incorporates the inclusion of the mind, body, spirit, and self-awareness during treatment, as well as connection to community through an emphasis on the utilization of community resources. The intervention aims to increase the coping skills of participants and reduce the chance of relapse by emphasizing values such as respect, care, integration, and healing of self [38]. Seeking Safety has been translated into 14 languages and evaluated in over 40 published studies [39]. The treatment has shown positive results and is the only model for PTSD/SUD thus far to impact both PTSD and SUD [39]. Also, Seeking Safety has been implemented with Indigenous peoples in Canada and showed positive results [40]. Importantly, the perspective of SS is convergent with Indigenous traditional healing methods. Due to the content and delivery method of SS, the program complements traditional teachings such as holism, relational connection, spirituality, cultural presence, honesty, and respect [15, 16, 24, 41].

Benbowopka Treatment Centre started in 1991 as a 12-Step Alcoholics Anonymous model of intervention to address alcohol addiction that was prominent in many First Nations communities during that time. However, the onset of prescription drug misuse in First Nations communities shifted the need for addictions treatment towards harm reduction models of service. This has prompted Benbowopka Treatment Centre to go through a significant transformation over the last 36 months in regard to ensuring its services are better able to address the SUD needs of First Nations communities.

The abstinence model of service that was being delivered at Benbowopka Treatment Centre was excluding many individuals who were seeking residential addictions treatment for problems related to prescription opioids and other drugs. Individuals who were on prescribed medication, including opioid agonist treatment, by their physician to address SUD or mental health challenges were not eligible for admission to Benbowopka Treatment Centre because of its abstinence-based model of service. In 2014, Mamaweswen North Shore Tribal Council directed Benbowopka Treatment Centre to move forward with a plan for the realignment of its services to a harm reduction model of service that would follow the best practice strategies recommended for addictions treatment. Thus, the implementation of the Indigenous Healing and Seeking Safety (IHSS) approach at Benbowopka for Indigenous patients with a history of IGT and SUD was initiated in 2016.

The Mamaweswen (North Shore Tribal Council) and the Benbowopka Treatment Centre represent seven member communities (Batchewana, Garden River, Thessalon, Sagamok, Mississauga, Atikameksheng, and Serpent River) on the North Shore of Lake Huron. Benbowopka treats approximately 90 patients per year in a residential treatment program. The program has high-quality retrospective data based on standardized assessment screening tools routinely used by the Drug and Alcohol Treatment Information System and the National Native Alcohol and Drug Abuse Program.

This study will aim to evaluate the effectiveness of the validated treatment model (IHSS) for the treatment of Indigenous patients with a history of IGT and SUD in a four-week residential treatment centre. Study findings will be used to inform trauma and SUD residential treatment programming and implementation for Indigenous communities across Canada. Hopefully this work will contribute to the field of community-based trauma and addiction programming by addressing objectives that consider:*The patient perspective* does patient satisfaction improve when IHSS methodology for treatment of trauma and SUD replaces an abstinence-focused approach?*The program perspective* do program completion rates improve following the implementation of IHSS intervention?*The community perspective* does the revised program serve a broader range of community members requiring treatment for SUD and IGT? Does the impact of residential addiction treatment on reducing broader health care utilization (through reduced substance use related emergency room presentations and hospital admissions in the year following treatment completion) increase following IHSS implementation?

## Methods

### Aim

The aim of this study will be to determine whether patients who are treated with the IHSS model will have improved treatment satisfaction (increase of 10% over pre-intervention rates), improved treatment completion (increase of 10% over pre-intervention rates), and a greater reduction in health system usage (substance use related presentations to emergency room and hospital admissions) at one-year follow-up compared to those treated within the abstinence-based model (decrease of 10% over pre-intervention rate).

### Design

We will conduct a pre/post Quasi Experimental Community trial in northern Ontario, Canada, comparing historical treatment outcomes for past Benbowopka patients to outcomes following the implementation of IHSS treatment for Indigenous patients with a history of IGT and SUD. We will conduct a quantitative and qualitative analysis to understand the differences before and after the intervention is implemented. The pre-IHSS intervention study window will span over 36 months (April 1, 2013–March 31, 2016; *n* = 343), and the post-IHSS intervention study window will span the 27 months post-IHSS implementation (January 1, 2018–March 31, 2020; *n* > 300). We conducted an a-priori sample size calculation for our study with an anticipated effect size of 0.5, and probability level of 0.05. To have appropriate statistical power of > 80%, we would need 65 patients in each group. With the anticipated sample sizes of 300 pre and post-implementation, we have enough statistical power to confidently evaluate our outcomes.

All patient data will be anonymized at the time of data entry. Propensity score matching will be undertaken to evaluate the association between the IHSS treatment and long-term outcomes. The National Native Alcohol and Drug Abuse Program (NNADAP) tool will be used to analyze the program objective; that is, whether completion rates improve following the implementation of the IHSS intervention. Additionally, a Client Quality Assurance Survey will be utilized to determine patient satisfaction.

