### Setting of the study

Benbowopka treats approximately 90 patients per year in a residential addiction treatment program in Blind River Northern Ontario. The study periods will include pre-intervention (April 1, 2013–March 31, 2016) and the post-IHSS intervention study window spanning the 27 months post-IHSS implementation (January 1, 2018–March 31, 2021; *n* > 300). Time periods will be chosen to allow analysis by both calendar year and fiscal year. On every 28-day treatment cycle, participants will be recruited and informed by the staff at Benbowopka about the study and, if interested, a consent will be obtained. The data collection will include data from patients initiating treatment at Benbowopka during the study window. Patient follow-up will occur in the year following treatment completion and/or discontinuation. Anonymized patient records will be linked via Ontario Health Insurance Plan (OHIP) number to the administrative health data at the ICES. ICES, formally known as the Institute for Clinical Evaluative Sciences, is an independent research institute that collects and analyzes data on publicly funded health services for research. The data will be queried in the one year following completion or discontinuation of IHSS at Benbowopka to ascertain the impact of substance use on health outcomes including hospitalization, emergency department visits and opioid-related overdose. For patients with multiple admissions, the date of first admission will serve as the index date for health outcomes evaluation.

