### Training

Wellness, training, and capacity building will be the cornerstones of this research. Clinicians at Benbowopka were trained in the IHSS methodology (beginning January 2016) and IHSS is now routinely delivered to patients.

The five days of training on the IHSS program incorporates all of the elements of an integrative Two-Eyed Seeing and blended approach [45]. The training consists of didactic, experiential, and small-group learning. During the training the clinicians engage in IHSS sharing circle sessions such as Post Traumatic Stress Disorder (PTSD), taking back your power, setting boundaries in relationships, dealing with anger, and taking good care of yourself [46]. The design and delivery of this training is consistent with previous experience training IHSS facilitators by this research team [36, 47]. During these sharing circles the Elder offers a Grandfather teaching, Indigenous spiritual and traditional sayings, smudging, and/or prayers. The teachings of the Seven Grandfathers, also known as either the Seven Teachings or Seven Grandfathers, are a set of teachings on human conduct toward others. They include the concepts of wisdom, love, honesty, respect, bravery, humility, and truth [48]. The day starts with didactical presentations until lunchtime, and in the afternoon the clinicians engage in an actual IHSS sharing circle facilitated by the first researcher and an Elder. The clinicians have opportunities to ask questions, and through this in-depth discourse evolve. Day three and four focus on substance use disorders and exploration of information in the Seeking Safety manual. In-depth discussions help clinicians understand how the Seeking Safety sessions are offered as well as the integration of traditional healing practices. The last day of training focuses on vicarious traumatization, practice sessions, planning and implementation.

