### Data collection

The historical program data will be collected from Benbowopka’s records from January 2013 to March 2016 (end of the 2015 fiscal year). The data will be divided into fiscal year and intake period at the request of Benbowopka. Historical demographic data for each intake period will be found in the “Client Information Summary” folders in Benbowopka’s archive room.

We will use the Drug Use Screening Inventory (DUSI) to collect data on patients during the program. The DUSI and a revised version (DUSI-R) were developed by the Center for Addiction and Mental Health (CAMH) to identify consequences of alcohol and drug involvement [49]. The DUSI is a 149-item multidimensional instrument that quantifies not only involvement with drugs and alcohol, but also associated problems in the areas of mental health and psychosocial domains. The DUSI-R consists of 159 items. The following variables will be collected: name, health card number, date of birth, postal code, status card number, gender, date of admission to the program, date of discharge, program completion (Y/N), Indigenous (Y/N), status First Nation (Y/N), on reserve (Y/N), primary substance, and secondary substance(s). Drug classes from primary and secondary substances will be further divided into a sub-substance category. Any pertinent notes will also be included in the data.

The original data will include drug classes used by Benbowopka (i.e. alcohol, narcotics, prescription drugs, solvents/inhalants, and other). The revised data will be organized by the drug class preference of the research team (i.e. alcohol, cannabis, stimulants, opioids, depressants, hallucinogens, inhalants/solvents). Some drug names will be changed to ensure cohesion (e.g. brand to generic names, acid to LSD, etc.).

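### The pre-IHSS control window includes January–March 2016, after IHSS training had begun, so up to about 8% of controls may have been exposed

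*Protocol article*

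**What the plan says.** The control period is defined twice, with the same dates. Design: "The pre-IHSS intervention study window will span over 36 months (April 1, 2013–March 31, 2016". Setting of the study: "The study periods will include pre-intervention (April 1, 2013–March 31, 2016". Design attaches the cohort size directly to those dates: "April 1, 2013–March 31, 2016; *n* = 343".

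Two other sections date the arrival of IHSS:

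- Training: "Clinicians at Benbowopka were trained in the IHSS methodology (beginning January 2016) and IHSS is now routinely delivered to patients". The course lasts five days.
- Background: implementation "at Benbowopka for Indigenous patients with a history of IGT and SUD was initiated in 2016". No month is given.

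The post-IHSS window opens on January 1, 2018. Data collection takes historical "records from January 2013 to March 2016 (end of the 2015 fiscal year", which starts three months before the control window. Setting of the study says the periods are chosen so that results can be analysed by calendar year and by fiscal year.

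**The concern.** The Aim compares IHSS patients with patients treated under the abstinence-based model. A historical control group serves that comparison only if its members were treated before the new model reached them. January–March 2016 is labelled pre-IHSS, yet it lies after staff training began and in the year in which implementation was initiated.

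The design leaves a gap of 21 months (April 2016–December 2017) between the two windows, but all of it comes after this quarter. Nothing in the article says that patients admitted in the quarter received only the former program, and nothing sets the quarter aside.

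Any IHSS exposure among controls would pull the two groups together. The Abstract names sex/gender, age and substance use type as matching characteristics. Matching on these would not remove the problem, because none of them records when a patient was treated.

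**Working it through.** **Inputs**

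- Control window April 1, 2013–March 31, 2016, n = 343 (Design).
- Training from January 2016 (Training); initiation in 2016, month not given (Background).
- Throughput of about 90 patients per year and a 28-day cycle (Setting of the study).
- Target improvement in completion of 10% (Aim). The article does not say whether this is absolute or relative; 10 percentage points is assumed here.

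**1. Length of the window.** April 2013 to March 2016 is 36 months (1,096 days). The stated figure reproduces.

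**2. Share of the window after training began.** January 1–March 31, 2016 is 3/36 = 8.3% of the months, or 91/1,096 = 8.3% of the days.

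**3. Patients involved.**

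- Even intake over the window: 343 × 3/36 = 28.6, about 29.
- Stated throughput: 90 × 3/12 = 22.5, about 22.

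**4. Dilution.** Let f be the share of controls in the quarter and e the fraction of the full IHSS effect they received. The observed difference is then the true difference × (1 − f × e). For a true difference of 10 points and f = 3/36:

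- e = 1: 10 × (1 − 0.0833) = 9.2 points, a loss of 0.8.
- e = 0.5: 10 × (1 − 0.0417) = 9.6 points, a loss of 0.4.
- e = 0: no loss.

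**5. Power.** The control completion rate is not given, so rates of 40% to 80% are assumed. The test is an unmatched two-sided comparison of two proportions at 0.05, with a true 10-point difference. This illustrates scale only and does not reproduce the planned matched analysis.

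| Controls vs IHSS | Exposure of the quarter | Power, 40–80% control rate |
|---|---|---|
| 343 vs 300 | none | 72–95% |
| 343 vs 300 | half effect | 68–93% |
| 343 vs 300 | full effect | 65–91% |
| 314 vs 300 (quarter dropped) | not applicable | 70–94% |

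Dropping the quarter costs about 1 to 2 points of power if nobody was exposed. It gains about 3 to 6 points if everybody was.

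On the plan's own standardised effect of 0.5, full dilution gives 0.5 × (1 − 0.0833) = 0.46, and power with 300 per group stays above 99%.

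**6. The January 2013 start of extraction.**

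- Calendar years 2013–2015: January 2013–December 2015 (36 months).
- Fiscal years 2013–2015: April 2013–March 2016 (36 months).
- Both together: January 2013–March 2016 (39 months).

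The combined span is exactly the period from which records are collected.

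**The case against.** Training is not delivery. The course could have run in the first quarter of 2016 and delivery could have started in April, with the new fiscal year. All the stated dates would then agree. The article also refers to a detailed timeline in an appendix that is not shown and may settle the matter. This stands, and it limits the point to possible exposure.

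A reader might go further and infer that the control group was contaminated. The documents do not support that: no section says a patient received IHSS before April 2016.

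A reader might also infer from the January 2013 extraction start that the months behind n = 343 are unclear. That does not hold either. Design ties this number to April 2013–March 2016, and Data collection gives no competing number. At about 90 patients per year, 36 months would give 270 and 39 months about 293. Neither matches 343, so the throughput figure does not point to a different window. The earlier start is most plausibly a wider extraction covering both calendar and fiscal years, although the article does not say so.

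Finally, the effect is small, and moving the window disturbs the fiscal-year breakdown that the treatment centre asked for. Both are fair. They favour a light remedy but do not justify leaving the quarter unexamined.

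**Conclusion.** The point holds as a modest design weakness. The control window extends three months past the start of IHSS training, and the article neither gives the month of first delivery nor treats those months as transition.

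Up to 8.3% of the window, about 22 to 29 patients, could be affected. The resulting bias would run toward no difference, by at most about 0.8 of a 10-point effect.

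That ceiling assumes even intake and the full IHSS effect in every patient from the first day of January 2016. This is unlikely, because training only began that month. The true figure may be zero. The assumption that IHSS improves outcomes is the plan's own.

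**What to change.** State the date on which patients first received IHSS, and treat January–March 2016 as transition, in one of two ways:

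1. **Move the window** to January 1, 2013–December 31, 2015. It remains 36 months, ends before training began and uses records already being extracted. Recount n and use the same dates in the Abstract, Design, Setting of the study and Data collection. The cost is a truncated fiscal 2015 and a three-month fragment of the preceding fiscal year in the fiscal-year breakdown.
2. **Keep the fiscal-year window** and pre-specify a sensitivity analysis excluding patients in treatment from January 2016. The cost is about 8% fewer controls in that analysis (343 − 29 = 314).

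Under either option, say how patients admitted in December 2015 and still in residence on January 1, 2016 are handled. With a 28-day cycle this concerns at most about 343 × 28/1,096 ≈ 9 further patients.

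Add one sentence to Data collection explaining why records are extracted from January 2013. If, as seems likely, the reason is to cover both calendar and fiscal years, say so.

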### Study population

We will only include data from first-time patients initiating treatment at Benbowopka, meaning that there will be no previous history of treatment at this center. It is common for patients to cycle between treatment and relapse. Studies have shown that multiple treatment attempts are associated with a higher likelihood of positive outcome [32]. Therefore, we will only include first-time patients to eliminate bias associated with cases involving multiple treatment attempts.

Benbowopka’s residential treatment program collects individual-level data based on standardized assessment screening tools routinely used by the Drug and Alcohol Treatment Information System and the National Native Alcohol and Drug Abuse Program. The cohort for this study will be created by using anonymized patient records from the Ontario Health Insurance Plan (OHIP) number. We will link the OHIP number to the administrative health data at ICES in order to be able to evaluate broad health outcomes for patients after they completed the treatment program. ICES routinely links partner data to its core health systems data holdings. We will then query data in the one year following completion or discontinuation of IHSS at Benbowopka to ascertain *Impact of Substance Use on Hospital Costs* as defined by the Canadian Center on Substance Abuse [42]. ICES linkage will enable virtual follow-up of Benbowopka patients for health systems usage. A detailed timeline can be found in the appendix.

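### The post-IHSS window has two end dates a year apart under one 27-month label, and the stated n > 300 does not follow from the protocol's own intake rates for 27 months

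*Protocol article*

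**What the plan says.** The protocol article describes the post-intervention window in three places.

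- Abstract, Methods: "the post-Indigenous Healing and Seeking Safety intervention study window from 2018 to 2020; *n* > 300".
- Design: "post-IHSS intervention study window will span the 27 months post-IHSS implementation (January 1, 2018–March 31, 2020", with n > 300.
- Setting of the study: "post-IHSS intervention study window spanning the 27 months post-IHSS implementation (January 1, 2018–March 31, 2021; *n* > 300".

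On intake, Setting of the study says: "Benbowopka treats approximately 90 patients per year in a residential addiction treatment program". Background gives the same rate. Study population narrows the cohort: "We will only include data from first-time patients initiating treatment at Benbowopka". It also remarks: "It is common for patients to cycle between treatment and relapse". Setting adds that patients are asked for consent.

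For the pre-intervention period, Design gives 36 months (April 1, 2013 to March 31, 2016) with n = 343. Data collection starts the historical records in January 2013. The sample size statement in Design asks for 65 per group at an effect size of 0.5, then rests its assurance of adequate power on 300 patients before and 300 after. Propensity score matching pairs the two groups 1:1.

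**The concern.** Design and Setting cannot both be right about the window. It decides which admissions form the intervention cohort and the calendar date to which linked health data are needed. Follow-up is one year per patient, so that date falls around March 2021 or March 2022, plus up to one 28-day stay. The end date does not change the length of follow-up for any patient.

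The same n > 300 is attached to both end dates, although one span is twelve months longer. A count that does not move with the window is not visibly derived from it, so it needs checking against the intake rate. Because matching is 1:1, the smaller cohort caps the number of pairs, and an overstated post-intervention count overstates the size of the matched analysis.

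**Working it through.** **Inputs.** Window dates and n from Abstract, Design and Setting; about 90 patients per year from Background and Setting; 343 in 36 months from Design; effect size 0.5, significance level 0.05 and 65 per group from Design. The protocol does not say whether the test is two-sided; two-sided is assumed.

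**1. The plan's own sample size.** For two means at a standardised difference of 0.5, two-sided 0.05 and 80% power, the normal approximation gives 63 per group and the t-test 64. With 65 per group, power is 0.81. The stated 65 is reproduced.

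**2. Window lengths, counting whole months.**
- January 2018 to March 2020: 2 × 12 + 3 = 27 months.
- January 2018 to March 2021: 3 × 12 + 3 = 39 months.

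The 27-month label fits only the 2020 end date.

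**3. Intake rates in the protocol.**
- Stated: about 90 per year.
- Implied by the pre-window count: 343 / 36 × 12 = 114.3 per year.

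**4. Expected post-intervention patients (annual rate × months / 12).**

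| Window | At 90 per year | At 114.3 per year | Rate needed for 301 |
|---|---|---|---|
| 27 months | 202.5 | 257 | 301 × 12 / 27 = 133.8 per year |
| 39 months | 292.5 | 372 | 301 × 12 / 39 = 92.6 per year |

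Against 300, the 27-month window is short by (300 − 202.5) / 300 = 32.5% at the stated rate and by (300 − 257) / 300 = 14% at the implied rate. The 39-month window is short by 2.5% at the stated rate and above 300 at the implied rate.

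**5. First-time restriction.** The share of repeat patients is not given. Assuming 0% to 20%, the 90-per-year figures become 162 to 202.5 (27 months) and 234 to 292.5 (39 months). Refusal of consent, also not quantified, would lower them further.

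**6. Pre-intervention window.** 90 × 36 / 12 = 270, against a stated 343. Starting in January 2013, as Data collection does, makes the period 39 months and gives 292.5, still below 343. No stated period reconciles 343 with 90 per year.

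**7. Effect on the plan's power claim.** With 202 per group and effect size 0.5, power is above 0.99. The requirement of 65 is exceeded about threefold (202.5 / 65 = 3.1).

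**The case against.** The best defence is that the year in Setting is a one-digit slip. Design, the 27-month label (used twice) and the abstract's 2018 to 2020 all agree; only the 2021 in Setting is out of line. Study population also points to a timeline in an appendix that is not shown. This makes 2020 the likelier date, but it does not settle the matter, because 2020 is the reading under which n > 300 fits worst.

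Three stronger readings are tempting, and the documents do not support them.

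- A reader might infer that 300 is out of reach in either window. For 39 months, 292.5 is within the looseness of an approximate 90 per year before the restrictions apply, and the implied rate gives 372. Even for 27 months the accurate statement is that 300 is unsupported, not impossible. The two documented rates conflict with each other, and Background describes dropping an admission rule that had excluded people on prescribed medication, so intake may have changed.
- A reader might infer that the power claim collapses. On the plan's own basis it does not (step 7). Whether an effect size of 0.5 suits the 10% changes named in the Aim is a separate question, and no baseline rates are given from which to size a loss of power here.
- A reader might infer that the cohort will be picked after results are seen. Two end dates leave that possible, but nothing in the text suggests it.

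**Conclusion.** The point stands in this form. The intervention cohort is not uniquely defined: the two end dates differ by twelve months, which is about 90 to 114 admissions at the protocol's own rates. In the 27-month window, n > 300 is unsupported at both documented rates (about 203 or 257). It is plausible only in the 39-month window (about 293 or 372). Separately, 343 in 36 months does not agree with 90 per year (270).

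The consequences are an ambiguous cohort, an unsupported stated sample size and fewer possible matched pairs: at most about 203 or 257 in 27 months, rather than 300. The power claim does not fail on the plan's stated basis.

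The date conflict rests on no assumption. The counts assume steady intake at the stated or implied rate and, before step 5, that every patient is a first-time patient who consents.

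**What to change.** Before any outcome linkage:

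1. State one end date for the post-intervention window in the abstract, Design and Setting, and make the month count match it.
2. Replace n > 300 with the actual or projected number of first-time admissions in that window.
3. Reconcile 343 with 90 per year by saying whether each figure counts admissions or first-time patients, and over which months. Settle whether the historical period starts in January or April 2013.
4. In the power statement, replace 300 before and after with the expected number of matched pairs.

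The cost is a wording amendment and a count from the centre's admission records. The stated sample size may become smaller.
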